### 3.12. Statistical analysis

Categorical variables will be compared using the Chi^-^square test or Fisher’s exact test. Normally distributed quantitative variables will be compared using the Student *t* test or an analysis of variance (ANOVA). Non^-^normally distributed quantitative variables will be analyzed using the non^-^parametric Wilcoxon or Kruskall^-^Wallis tests. Statistical tests for repeated measures will be used for before^-^ after comparisons (paired Student *t* test or paired Wilcoxon test, 1^-^way ANOVA with repeated measures or Friedman test).

The primary outcome will be described using the mean and the 95% confidence interval of the mean. The temporal trend of preoperative, intraoperative, and postoperative BG variability will be described by the mean and the 95% confidence interval of the mean of each variable describing BG variability and figured as boxplot. The relationship between preoperative and postoperative BG variability, between BG variability and the ANS activity and between the postoperative BG variability and the blood and urinary level of biomarkers of inflammation and endothelial function will be investigated using the Pearson or the Spearman correlation coefficient and univariate linear regression models and presented on adequate figures.

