## 2. Objectives

The primary objective is to describe the relationship between baseline (preoperative) and postoperative BG variability within 48 hours after surgery.

Secondary objectives are: to describe the relationship between baseline and postoperative BG variability within 48 hours after surgery according to the diabetic status and to the type of surgery; to describe the relationship between the preoperative activity of the ANS and the baseline BG variability; to describe the relationship between the preoperative activity of the ANS and the postoperative BG variability within 48 hours after surgery; to describe the relationship between postoperative BG variability within 48 hours after surgery and the postoperative activity of the ANS within 48 hours after surgery; to describe the relationship between postoperative BG variability within 48 hours after surgery and the diabetes phenotype; to describe the relationship between postoperative BG variability within 48 hours after surgery and the urinary and blood level of biomarkers of inflammation and of endothelial dysfunction; and to describe the morbidity and the mortality within 30 days after surgery.

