### 3.9. Laboratory measurements

Blood and urinary levels of biomarkers of inflammation (IL-2, IL-6, IL-10, TNF-alpha, 8-iso^-^prostanglandin^-^F_2*α*_) and of endothelial function [Endocan, angiopoietin^-^1 (Ang^-^1), angiopoietin^-^2 (Ang^-^2), vascular endothelial (VE)^-^cadherin] will be measured from blood and urinary samples performed the day before surgery, on arrival in the ICU and at 24 hours and at 48 hours after admission in the ICU. Additional blood and/or urinary analysis will be performed if necessary, depending on the hypotheses formulated from the results of the study.

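### For secondary measures with three or more time points, the named one-way repeated-measures tests drop incomplete patients and have no group term; a mixed model on the same data would serve better

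*Protocol article*

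**What the plan says.** Section 3.12 of the protocol article sets out three families of methods.

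- **Repeated measurements.** "Statistical tests for repeated measures will be used for before^-^ after comparisons". The tests listed are the paired t test or paired Wilcoxon test for two values, and "1^-^way ANOVA with repeated measures or Friedman test" for more than two. None is tied to a named endpoint.
- **Other comparisons of quantitative variables.** Student t test or ANOVA, or Wilcoxon or Kruskal-Wallis. These are listed separately and are not combined with time.
- **Relationships.** Pearson or Spearman correlation and "univariate linear regression models".

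Two secondary measures have more than two time points. Biomarker samples are "performed the day before surgery, on arrival in the ICU and at 24 hours and at 48 hours after admission in the ICU" (section 3.9), which makes four times. Section 3.12 also mentions "The temporal trend of preoperative, intraoperative, and postoperative BG variability", three periods, but assigns it means with 95% confidence intervals and boxplots rather than a test. The design has four groups of 30 (sections 3.2 and 3.11).

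**The concern.** Two properties of the one-way tests fit this design poorly.

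First, classical repeated-measures ANOVA and the Friedman test need a complete row for each patient. A patient with three of four samples contributes nothing, although three values were measured. This loses precision. It can also distort the time course if the patients who miss samples differ from the rest.

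Second, time is the only factor. The tests can say whether a biomarker changes over time, but not whether it changes differently in insulin-requiring diabetic, non-insulin-requiring diabetic and non-diabetic patients, or by type of surgery. The relationship models do not supply that term, since each has a single covariate.

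At stake are the efficiency and usefulness of the secondary repeated-measures analyses. The main result of the study is not at stake.

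**Working it through.** **The plan's own figure.** Section 3.11 gives SD 8.2, alpha 0.05, a 95% interval range of 6.12 and 30 patients per group. For one mean, the full width is 2 × t(0.975, n−1) × SD/√n. With n = 30 this is 2 × 2.045 × 8.2/√30 = 6.124, which agrees with 6.12 up to rounding. That calculation concerns the pre-post difference in CV, with two values per patient. Nothing below changes it.

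**Complete rows.** Inputs: k = 4 times (section 3.9) and 120 patients in four groups of 30 (section 3.11). The per-time loss d is not in the document, so 2% to 15% is an assumption. If losses are independent across times:

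- share of patients with complete rows = (1−d)^4
- observed values expected = 480 × (1−d), of which complete rows hold 480 × (1−d)^4
- share of measured values discarded = 1 − (1−d)^3

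| Loss per time (assumed) | Complete share | Of 120 | Of 30 | Values observed | Values in complete rows | Measured values discarded |
|---|---|---|---|---|---|---|
| 2% | 0.922 | 110.7 | 27.7 | 470 | 443 | 6% |
| 5% | 0.815 | 97.7 | 24.4 | 456 | 391 | 14% |
| 10% | 0.656 | 78.7 | 19.7 | 432 | 315 | 27% |
| 15% | 0.522 | 62.6 | 15.7 | 408 | 251 | 39% |

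Independence is unfavourable to the plan. At the other extreme, the same patients miss all four samples. The complete rows are then 120 × (1−d) = 117.6, 114, 108 and 102, and no measured value is discarded. The abstract lists only three sampling times. With k = 3 and independent loss of 5% or 10%, 0.95^3 × 120 = 102.9 or 0.90^3 × 120 = 87.5 patients are complete.

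**Group term.** With four groups and four times, a group-by-time comparison has (4−1) × (4−1) = 9 degrees of freedom. The one-way tests contain none of these.

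**Rough simulation.** 80 runs per scenario; four groups of 30, four times, within-patient correlation 0.5, time means rising to 0.25 SD. All settings are assumed. The mixed model had a random patient effect.

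| Loss per time, at random | Power for time: RM-ANOVA | Power for time: mixed model | SD of last-minus-first estimate: RM-ANOVA | Mixed model |
|---|---|---|---|---|
| 0% | 0.725 | 0.725 | 0.094 | 0.094 |
| 5% | 0.71 | 0.78 | 0.097 | 0.098 |
| 10% | 0.56 | 0.71 | 0.121 | 0.102 |

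Each power figure carries about ±0.10. The mixed model cost nothing with complete data, and a gain in precision is visible only at 10% loss. With a 0.6 SD group-by-time effect in one group at the last two times and 10% loss, the mixed model detected it in 80% of runs. That figure is rough: without such an effect, the same test rejected in 2.5% to 12.5% of runs, depending on the scenario. In one scenario where drop-out depended on an earlier observed value, both methods gave the same average last-minus-first change (0.266). These runs therefore do not demonstrate bias in that contrast.

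**The case against.** Much of the opposing case is sound.

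- **A reader might infer that the plan cannot compare change between groups.** It can. For a two-value measure, ANOVA or Kruskal-Wallis on the pre-post change does this, and with complete pairs that ANOVA is the same as the group-by-time F test. The same device could be applied to a biomarker one later time at a time. Only a joint analysis over three or more times is absent.
- **A reader might infer that a stated objective goes unanswered.** Section 2 does ask for results "according to the diabetic status and to the type of surgery", but that objective concerns baseline and postoperative glucose variability. The biomarker objective is a relationship with postoperative glucose variability, handled by correlation and regression. For biomarkers, the group-by-time term is an improvement and not a stated requirement.
- **A reader might expect separate tests in each group, with their p-values compared.** The article does not say this will be done.
- **Missingness may be low.** Three of the four samples fall in the first 48 hours, when every patient is to stay in the ICU (section 3.5), and the other falls on the day of admission. Sensor loss (section 3.6) does not bear on blood and urine samples.
- **The replacement has limits.** A single random patient effect forces equal correlation between all times, much as repeated-measures ANOVA does. Nine biomarkers in two fluids could mean 18 models.

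It could also be said that modelling detail belongs in an analysis plan that is not shown. That plan might specify a better model, but the article itself names these tests, and the comment is on the tests named. What stands is that they need complete rows and have no group factor, and the objections do not alter either property.

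**Conclusion.** The point holds as a modest, inexpensive improvement to secondary analyses with three or more time points, chiefly the biomarkers. That the multi-time tests are meant for the biomarkers is an inference, because section 3.12 does not assign them.

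Under the assumed independent losses of 2% to 15%, between about 111 and 63 of 120 patients would enter the tests. If losses cluster within patients, the number is higher. If nothing is missing, the first half of the point has no effect and only the absent group-by-time term remains.

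The documents do not support a claim that the primary outcome, its confidence interval or the sample size is compromised. Nor do they support a claim that results will be biased, since that depends on why samples are missed, which the article does not address. There is no contradiction in the text; a better method is available for data already planned.

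**What to change.** In section 3.12, for measures with three or more time points, replace the one-way repeated-measures ANOVA and Friedman test with a linear mixed model for each measure, log-transformed where skewed:

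- fixed effects for time, group and group-by-time;
- a within-patient covariance not forced to be equal across times (for four times, 4 × 5/2 = 10 parameters), falling back to a random patient effect if the model does not converge;
- all available observations included;
- group-specific changes from the preoperative value reported with 95% confidence intervals, which suits objectives that are framed as descriptive.

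Friedman may be kept as a sensitivity analysis. Paired tests, and ANOVA or Kruskal-Wallis on the change, can stay for two-value measures.

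The cost is a change of analysis wording and slightly more modelling work, with no extra patients, samples or procedures. The model assumes data are missing at random, which is weaker than what a complete-row analysis generally needs, but it does not cure data missing not at random.

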## 1. Introduction

Blood glucose (BG) variability in diabetic and non-diabetic patients is independently associated with increased morbidity and mortality in the intensive care unit and after cardiac events.^[1–3]^ In cardiac surgery patients, BG variability is reported to be associated with severe postoperative complications – leading to an increase length of intensive care unit (ICU) stay – regardless of the quality of BG control obtained during the perioperative period.^[4–6]^

Several hypotheses have been raised to explain the deleterious effect of BG variability observed in diabetic patients. Basal state BG variability seems to depend on the diabetes phenotype and to differ between people with or without diabetes.^[7,8]^ Furthermore, some studies suggest an association between BG variability and the activity of the autonomic nervous system (ANS).^[9–13]^ Finally, other studies highlight that the deleterious effect of BG variability includes increased oxidative stress, endothelial dysfunction, and cell apoptosis.^[14–16]^ However, no study has specifically addressed this issue in cardiac surgery patients and the underlying mechanisms contributing to increased perioperative BG variability and to its deleterious impact remain unclear.

The aim of this study is to investigate whether postoperative GV could be related to preoperative GV and/or to perioperative alteration of the ANS activity in diabetic and non-diabetic cardiac surgery patients and the relationship between postoperative GV and blood and urinary level of inflammation and endothelial dysfunction biomarkers.

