At the end of surgery, all patients will be admitted to the intensive care unit (ICU) and will stay during at least the first 48 postoperative hours, and then will be discharged to the ward. During the ICU stay, all patients will undergo the same standard monitoring (Carescape B850 monitor, General Electric Healthcare, USA) as in the operating room, that is the continuous monitoring of at least heart rate, electrocardiogram, pulse oximetry and invasive arterial pressure. Sedation will be stopped, and the patients will be extubated as soon as possible according to the usual criteria (i.e., free of sedation, normothermic, fulfilling specified respiratory criteria). Postoperative analgesia will consist in intravenous paracetamol 15 mg/kg 4 times a day and patient^-^controlled analgesia with morphine. Intravenous glucose infusion will be administered at a constant rate of 4.0 to 4.5 g/hours until oral feeding could be resumed and at least during the first 48 postoperative hours. BG control will be managed according to a validated and published dynamic insulin therapy protocol,^[18]^ adapted from Goldberg *et al*^[19]^ and implemented in our ICU since December 2005. Briefly, hourly BG measurement starts with the skin incision. All BG values are obtained, from glucose meter readings (Optium Xceed; Abbott Diabetes Care, UK) measured from arterial blood samples taken from the arterial line. The target BG level is 100 to 139 mg/dL (5.5–7.7 mmol/L). Intravenous insulin infusion starts with the first BG value > 139 mg/dl (7.7 mmol/L). After an initial bolus of insulin based on the BG value, the infusion rate is adjusted based on 3 parameters: the current BG value; the previous BG value; and the current insulin infusion rate. When hypoglycemia occurs, the insulin infusion is stopped and intravenous dextrose 30% is administered (10 mL if BG is between 50 and 74 mg/dL [2.7–4.1 mmol/L] and the patient is asymptomatic; 20 mL if BG is between 50 and 74 mg/dL [2.7–4.1 mmol/L] and the patient is symptomatic or if BG is <50 mg/dL [<2.7 mmol/L]). The insulin infusion is resumed 1 hour after the first BG value > 100 mg/dL (>5.5 mmol/L) at a lower rate (75% of the original rate if BG is between 50 and 74 mg/dL [2.7–4.1 mmol/L] and 50% of the original rate if BG is <50 mg/dL [<2.7 mmol/L]). Depending on the patient’s clinical condition, oral intakes are initiated as soon as possible, and the intravenous insulin infusion is replaced by subcutaneous insulin when necessary.

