### 3.6. Assessment of perioperative blood glucose variability

After written informed consent is obtained, a subcutaneous glucose sensor Abbott® FreeStyle Libre Pro will be applied in the fatty part of the back of the upper arm of included patients, as recommended by the manufacturer. The Abbot® FreeStyle Libre Pro glucose sensor will allow to measure the baseline BG variability during at least 2 consecutive days prior to surgery using the following parameters: the standard deviation (SD) of BG, the coefficient of glycemic variability (CV) (defined as the ratio of the SD on the mean BG expressed as a percentage), the mean of the daily differences between the higher and the lower values of BG (MAGE), the glycemic lability index and the glycemic penalty index. In case of accidental removal of the sensor during this period or delayed surgery > 14 days after the inclusion, patients will be informed to bring back the sensor the day before surgery so that all blood glucose measurements stored in the sensor can be collected.

The subcutaneous glucose sensor Abbott® FreeStyle Libre Pro will be changed the day before surgery and applied in the same area to measure postoperative BG variability up to 7 days after surgery using the same parameters as preoperatively.

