### 3.8. Outcome measures

The primary outcome will be the mean difference between the preoperative (baseline) and the postoperative CV, and its 95% confidence interval, measured using the subcutaneous glucose sensor Abbott® Free Style Libre Pro.

Secondary outcomes will: the preoperative and postoperative BG variability, quantified by the preoperative and postoperative values of: the SD of BG, the CV, the MAGE, the glycemic lability index and the glycemic penalty index; the preoperative and postoperative activity of the ANS, quantified by the preoperative and postoperative values of: the COMPASS 31 score, the LF, the HF, the LF/HF ratio, the RMSSD, the SDNN, the SDANN, and the pNN50; the diabetes phenotype, described by the preoperative fasting BG and glycosylated hemoglobin values; the blood and urinary levels of biomarkers of inflammation (IL^-^2, IL^-^6, IL^-^10, TNF^-^alpha, 8^-^iso^-^prostanglandin^-^F_2*α*_) and of endothelial function [Endocan, angiopoietin^-^1 (Ang^-^1), angiopoietin^-^2 (Ang^-^2), vascular endothelial (VE)^-^cadherin]; and postoperative morbidity and mortality at day 30 after surgery. Postoperative morbidity includes cardiac arrest, stroke, cardiac arrhythmia requiring therapeutic intervention, surgical wound infection, pneumonia, renal failure requiring dialysis, sepsis, surgical revision, readmission in the intensive care unit or in hospital.

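### The biomarker analysis is univariate and mean glucose is not an outcome, so an association seen with SD or the high-low range (MAGE) may reflect glucose level rather than variability

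*Protocol article*

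**What the plan says.** - **Analysis (3.12, Statistical analysis).** The relation "between the postoperative BG variability and the blood and urinary level of biomarkers of inflammation and endothelial function will be investigated using" Pearson or Spearman correlation and regression. The same sentence covers the other relationships, which "will be investigated using the Pearson or the Spearman correlation coefficient and univariate linear regression models". The article names no covariate and no multivariable model anywhere.
- **Outcomes (3.8).** The glucose measures are "the SD of BG, the CV, the MAGE, the glycemic lability index and the glycemic penalty index". Mean glucose is not among them.
- **Where mean glucose appears (3.6).** It enters only through CV, "defined as the ratio of the SD on the mean BG expressed as a percentage". The same section describes MAGE as an average of daily high-minus-low differences, which is a quantity in glucose units.
- **Other measures of level (3.8).** These are preoperative and serve as description: "the diabetes phenotype, described by the preoperative fasting BG and glycosylated hemoglobin values".
- **Motivation (1, Introduction).** Variability is said to go with complications "regardless of the quality of BG control obtained during the perioperative period", and cited work is summarised as showing that "the deleterious effect of BG variability includes increased oxidative stress, endothelial dysfunction, and cell apoptosis".
- **Glucose management (3.5).** All patients follow one insulin protocol: "The target BG level is 100 to 139 mg/dL".

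**The concern.** The introduction treats variability as something that matters apart from glucose level. The biomarker objective in section 2 is where the study looks at the proposed mechanism. Yet two of the five indices, SD and MAGE, are in absolute units. Of two patients with the same CV, the one with the higher postoperative mean has the higher SD, by the article's own definition of CV. If an inflammatory or endothelial marker responds to glucose level, a univariate regression on SD will pick up that response. Because mean glucose is neither a covariate nor a listed outcome, a reader of the results could not judge which explanation fits. What is at stake is the interpretation of one secondary objective; the primary outcome is not touched.

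**Working it through.** **Figures in the plan.** The article gives none for this analysis. Its only calculation (3.11) concerns the primary outcome and reproduces: the full 95% interval width at n = 30 with SD 8.2 is 2 × 2.045 × 8.2/√30 = 6.12. The present point does not alter it.

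**From the documents.** CV = SD/mean (3.6), so ln SD = ln CV + ln mean. There are 120 patients in four groups of 30 (3.11), and alpha is 0.05.

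**Assumed, because the documents give no values.**
- Between-patient SD of ln mean, s_m: 0.08 to 0.20.
- Between-patient SD of ln CV, s_c: 0.20 to 0.30.
- Correlation of marker with mean, r: 0.3 to 0.5.
- CV and mean are independent, and the marker depends on the mean only.

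The low end of s_m is tied to the 100 to 139 mg/dL target. If about 95% of patient means lay in that band, s_m would be about ln(1.39)/4 = 0.08. If means were spread evenly over the band, s_m would be ln(1.39)/√12 = 0.095.

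**Formulas.**
1. Correlation of ln SD with ln mean: r1 = s_m/√(s_m² + s_c²).
2. Correlation of ln SD with the marker, with no effect of variability: ρ = r1 × r.
3. Chance of p < 0.05: Φ(z − 1.96) + Φ(−z − 1.96), where z = atanh(ρ) × √(n − 3).

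| s_m / s_c / r | r1 | ρ | n = 120 | n = 30 |
|---|---|---|---|---|
| 0.08 / 0.30 / 0.3 | 0.258 | 0.077 | 13% | 7% |
| 0.08 / 0.20 / 0.4 | 0.371 | 0.149 | 37% | 12% |
| 0.15 / 0.20 / 0.4 | 0.600 | 0.240 | 75% | 25% |
| 0.20 / 0.20 / 0.5 | 0.707 | 0.354 | 98% | 48% |

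Example, third row: r1 = 0.15/√(0.0225 + 0.04) = 0.60 and ρ = 0.60 × 0.4 = 0.24. At n = 120, z = 0.2448 × √117 = 2.65, and Φ(0.69) = 75%. At n = 30, z = 0.2448 × √27 = 1.27, and Φ(−0.69) = 25%.

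Simulation of the same model agrees with these rates to within about 2 percentage points, on the log scale or with raw SD. It gives about 5% in every case for SD with ln mean as covariate.

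**CV under the same assumptions.** CV is independent of the mean and the marker depends only on the mean, so their correlation is 0 and the planned univariate CV regression rejects at about 5%.

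**What adjustment does.** Write marker = a + b ln SD + c ln mean. Substituting ln SD gives a + b ln CV + (b + c) ln mean. The adjusted coefficient of ln SD is therefore the coefficient that ln CV would have beside ln mean.

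**Not computed.** MAGE is argued from its units only. The article gives no formula for the lability and penalty indices, so how far they carry glucose level cannot be worked out from it.

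**The case against.** The strongest objections are these.

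- **CV is already in the plan.** It is the index of the primary outcome and is scaled by the mean. A marker associated with SD but not with CV would itself point to level. This stands, and it confines the point to the absolute-unit indices. A reader might infer that the planned analysis cannot tell variability from hyperglycaemia at all; the same assumptions that produce the false positives for SD show otherwise for CV. CV becomes affected only if CV and mean are correlated, on which the documents are silent.
- **The objective is to describe.** Section 2 promises a description of the relationship, and correlation provides that. The introductory remark on quality of control summarises literature on complications and is not an estimand for biomarkers. This also stands. A reader might infer that hyperglycaemia will be reported as an effect of variability, but nothing in the article commits the authors to that wording. What remains is that the description omits the obvious competing explanation.
- **The size is assumed.** The common insulin protocol narrows the spread of means, and 3.12 does not say that the analysis pools all 120 patients. Both points stand and are why the range is wide and the figures for 30 are shown. Neither brings the rate for SD to 5%.
- **Adjusting for the mean alone is partial.** Diabetes group and type of surgery differ by design and could relate to both variables. This is true, so an adjusted coefficient is still an association.
- **A journal article condenses.** Further models may sit in a fuller document. But the article does state the choice, univariate, and lists its glucose outcomes.

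**Conclusion.** The point holds for SD and, by its units, for the high-low difference called MAGE: a univariate association with a biomarker may reflect glucose level. It does not hold for CV unless CV and mean glucose are correlated.

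If a marker depends on mean glucose only, the false-positive rate for SD is roughly 13% to 98% in a pooled analysis of 120 and about 7% to 48% in a group of 30. Every input to those ranges other than the sample sizes and alpha is an assumption, so they show that the problem can be material, not how large it will be.

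The point concerns one descriptive secondary objective and calls for a modest change made before analysis.

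**What to change.** 1. In 3.8, add mean sensor glucose for the preoperative window and for the 48-hour postoperative window.
2. In 3.12, keep the univariate estimates. For each biomarker, add a regression on the variability index with mean glucose of the same window as covariate, and report the two estimates side by side.
3. State that an association with SD or MAGE will be attributed to variability separately from glucose level only if it holds in the adjusted model.

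**Cost.** Wording in two sections and one covariate. The mean is already needed to obtain CV, so there is no new measurement.

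**Downside.** Intervals for SD and MAGE widen because these indices correlate with the mean. For ln SD the standard error is multiplied by about 1/√(1 − r1²), which is 1.04 at r1 = 0.258, 1.25 at 0.60 and 1.41 at 0.707, before any gain from variance that the mean explains.

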### 3.2. Eligibility

Adult patients who undergo planned on-pump coronary artery bypass surgery or aortic valve replacement surgery in the University Hospital of Besancon, France (Centre Hospitalier Universitaire (CHU) de Besancon) will be eligible for inclusion.

Four groups of 30 patients will be studied: group 1, including insulin-requiring type 2 diabetic patients undergoing on-pump coronary artery bypass graft (CABG); group 2, including non-insulin-requiring type 2 diabetic patients undergoing on-pump CABG; group 3, including non-diabetic patients undergoing aortic surgical valve replacement; and group 4, including non-diabetic patient undergoing on-pump CABG.

Inclusion and exclusion criteria for the present study are listed below.

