### 3.11. Sample size calculation

Four groups of patients will be included to describe the relationship between preoperative (baseline) and early postoperative BG variability in diabetic (groups 1 and 2) and non^-^diabetic patients (groups 3 and 4), and between BG variability and the ANS activity in patients treated (groups 1, 2 and 4) or not (group 3) with beta^-^blockers: group 1, including patients with insulin^-^requiring type 2 diabetes mellitus undergoing planned on^-^pump CABG surgery; group 2, including patients with non^-^insulin^-^requiring type 2 diabetes mellitus undergoing planned on^-^pump CABG surgery: group 3, including non^-^diabetic patients undergoing planned aortic valve replacement surgery; and group 4, including non^-^diabetic patients undergoing planned on^-^pump CABG surgery.

No previous study has described the difference between the preoperative (baseline) and the early postoperative CV (primary outcome) in cardiac surgery patients. Thus, no assumption can be made on the expected value of the primary outcome. The sample size calculation was based in the expected measurement accuracy of the primary outcome in each group.

Considering an alpha risk at 0.05 and an estimated standard deviation of CV of 8.2 (basal state) (RE Pratley, 2018 Nov), we hypothesized that the 95% confidence interval range of the difference between the baseline and the early postoperative CV will be no more than 6.12 (conservative assumption considering that the variance will be lower because of the repeated measurement of CV in the same patients). A sample size of 30 patients per group was calculated using the PASS software (“Confidence Intervals for 1 Mean” method, Hahn, G.J. and Meeker, W.Q. 1991. Statistical intervals. John Wiley & Sons. New York).

Thus, the inclusion of a total sample size of 120 patients (30 patients per group) is planned.

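### Single-predictor correlations and regressions across four deliberately different groups can mix between-group with within-group association; group should be in the model

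*Protocol article*

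**What the plan says.** Section 3.12 names one set of tools for three relationships: pre- to postoperative glucose variability, variability to autonomic nervous system (ANS) activity, and postoperative variability to blood and urinary biomarkers. Each "will be investigated using the Pearson or the Spearman correlation coefficient and univariate linear regression models". That section mentions no group term, stratification or interaction for these relationships.

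Section 2 words the leading aim without groups: "The primary objective is to describe the relationship between baseline (preoperative) and postoperative BG variability within 48 hours after surgery". It then lists, as a separate secondary objective, "the relationship between baseline and postoperative BG variability within 48 hours after surgery according to the diabetic status and to the type of surgery".

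The sample is built by quota. Section 3.2 states: "Four groups of 30 patients will be studied". These are insulin-requiring type 2 diabetes with CABG (group 1), non-insulin-requiring type 2 diabetes with CABG (group 2), no diabetes with aortic valve replacement (group 3) and no diabetes with CABG (group 4).

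The article expects the groups to differ. The Introduction says: "Basal state BG variability seems to depend on the diabetes phenotype and to differ between people with or without diabetes". Section 3.11 adds that the ANS relationship is to be described "in patients treated (groups 1, 2 and 4) or not (group 3) with beta"-blockers.

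**The concern.** When a sample is assembled from groups with different means, an all-patient correlation has two parts: the association among patients of the same group, and the association among the group means. If diabetes raises both baseline and postoperative variability, the two will correlate over all 120 patients even if a patient's baseline says nothing about the postoperative value once group is known. If the group means run in opposite directions, a real within-group relationship can be hidden or reversed. The weight of each part is also set by the 30:30:30:30 quota, which is a design choice and does not reflect the mix of patients in practice.

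This bears on the primary objective, which is itself a relationship, and Section 3.12 offers no other tool for estimating it. A reader could take the coefficient as information about individual patients when some or all of it reflects diabetes status or type of surgery.

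**Working it through.** **The plan's own figure.** Section 3.11 derives 30 per group from SD 8.2 and a 95% interval of full width 6.12. With width = 2 × t(0.975, n−1) × SD/√n and n = 30, this is 2 × 2.045 × 8.2/5.477 = 6.12. It reproduces, and the present point does not depend on it.

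**Inputs.** Four groups of 30 (Section 3.2), SD of CV 8.2 and alpha 0.05 (Section 3.11). The article gives no group means, so all shifts below are assumptions, in units of the within-group SD.

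**Formula.** With equal groups and within-group SD 1 on both measures,

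pooled r = (C_b + ρ_w) / √[(1 + V_bx)(1 + V_by)],

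where V_bx and V_by are the variances of the group means, C_b is their covariance and ρ_w is the within-group correlation.

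**1. Aligned shifts, ρ_w = 0.** Put groups 3 and 4 at 0, group 2 at k and group 1 at 2k on both measures. Then V_b = k²(5/4 − 9/16) = 0.6875k² and r = V_b/(1 + V_b). At k = 0.5: 0.1719/1.1719 = 0.147. At k = 1: 0.6875/1.6875 = 0.407. Rejection rates are from simulation of 4 × 30 patients, 5,000 runs.

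| Step k (SD) | Pooled r | P<0.05, pooled |
|---|---|---|
| 0 | 0 | 5% |
| 0.25 | 0.04 | 7% |
| 0.5 | 0.15 | 36% |
| 0.75 | 0.28 | 89% |
| 1.0 | 0.41 | 99.8% |

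With group in the model, the mean r is about 0 in every row and rejection is 4.7% to 5.6%. Fisher's z gives a hand check at k = 0.5: √117 × atanh(0.147) = 1.60, so power is about Φ(1.60 − 1.96) = 0.36.

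**2. Only a gap between diabetic and non-diabetic patients, ρ_w = 0.** Gaps of 0.5, 1.0 and 1.5 SD on both measures give r of 0.06, 0.20 and 0.36, and rejection of 10%, 62% and 99%.

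**3. Postoperative shifts narrowed.** Keep baseline means of 0, 0, 0.5 and 1 SD, with postoperative shifts a quarter as large. Then C_b = 0.25 × 0.1719 = 0.0430 and V_by = 0.0107, so r = 0.0430/√(1.1719 × 1.0107) = 0.04, with about 7% rejection.

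**4. ANS, ρ_w = 0.** Here the patterns differ: variability is shifted in groups 1 and 2, and ANS activity in groups 1, 2 and 4 against group 3. For a shift d in each, |C_b| = 0.125d², V_bx = 0.25d² and V_by = 0.1875d². At d = 1: |r| = 0.125/√(1.25 × 1.1875) = 0.10, with about 20% rejection. At d = 0.5: |r| = 0.03125/√(1.0625 × 1.0469) = 0.03, with about 6%.

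**5. A true within-group relationship, ρ_w = 0.30, steps of 1 SD.** Means in the same direction: (0.30 + 0.6875)/1.6875 = 0.59. Means in opposite directions: (0.30 − 0.6875)/1.6875 = −0.23. The group-adjusted value stays at 0.30 in both.

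**6. Precision.** An r of 0.30 has a 95% interval of about −0.07 to 0.60 within one group of 30, and about 0.13 to 0.46 as a group-adjusted estimate on all 120.

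**The case against.** **Pooling is inferred.** Section 3.12 never says that the 120 patients are analysed together. Sections 2 and 3.11 show an intent to describe variability by diabetic status and the ANS relationship by beta-blocker treatment, and the sample is sized per group. Correlations run within groups would fit this text. That stands as a limit on certainty. But an ungrouped primary objective beside a separate by-group secondary one makes an all-patient coefficient likely, and the biomarker relationship has no by-group description at all.

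**The aims are descriptive.** A reader might infer that the study sets out to show that baseline variability or ANS activity causes postoperative variability, or that single-predictor models cannot serve the by-group objective. The article supports neither. It speaks of describing relationships in an observational study, and separate slopes by group with intervals would describe them. A crude association is also a legitimate quantity, since diabetes is part of what sets baseline variability. It answers a different question from the within-group slope, however, and should be labelled so.

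**The larger figures need aligned group means.** This is fair. The common insulin protocol and glucose infusion in Section 3.5 could narrow postoperative differences, and for ANS the article's own rationale separates different groups. Cases 3 and 4 show how small the effect may then be.

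**Detail may lie in an analysis plan that is not shown.** This would answer a gap. Here the article names the class of model, and a plan that added group would depart from the published wording.

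**Conclusion.** The point holds in a conditional form. Section 3.12 specifies one-predictor methods, the primary objective implies an all-patient analysis, and the groups were chosen to differ. The resulting coefficient can therefore combine between-group with within-group association, and may be inflated, attenuated or reversed.

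The size is not known from the article. For pre- and postoperative variability with no within-group relationship, it ranges from negligible (r about 0.04 at aligned steps of 0.25 SD) to large (about 0.41 at 1 SD). For ANS under the article's grouping rationale, it is modest: |r| of about 0.03 to 0.10 at 0.5 to 1 SD.

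A reader might conclude that the study is bound to report group differences as patient-level relationships, or that its main result is compromised. The first requires group means to differ on both variables. The article supports this for baseline variability but gives no postoperative figures. The second fails because the declared primary outcome in Section 3.8 is the mean difference in CV with its confidence interval, which is not a correlation and is untouched. This is a worthwhile correction to the analysis wording, not a fault in the design.

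**What to change.** In Section 3.12, replace the univariate regressions with linear models that include the four-level group as a fixed factor, for example postoperative CV on baseline CV plus group, and likewise for the ANS and biomarker models. Report group-adjusted (partial) Pearson or Spearman coefficients beside any all-patient coefficient, and label the latter as unadjusted.

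For the objective worded "according to the diabetic status and to the type of surgery", report the slope in each group with its 95% confidence interval, for example from a model with a baseline CV by group interaction.

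The cost is wording and 3 degrees of freedom out of 120, or 6 with the interaction, and no extra patients. Group-specific slopes at n = 30 will be imprecise, as the interval of −0.07 to 0.60 around r = 0.30 shows, and should be presented as descriptive.
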